## Methods/design

### Design and sample size

This trial will be a multicenter, prospective, parallel-group randomized controlled trial. Participants will be assigned either to a group receiving nutritional guidance (once every 3 months) or to a group not receiving nutritional guidance. We chose 3-monthly visits because nutritional guidance typically continues for about 6 months. In addition, a previous study reported that frequent visits have a greater effect on weight gain and that follow-up is needed at least once every 3 months [15]. Participants will be enrolled for 3 years after the trial is approved by the Central Ethics Review Committee. The total duration of the trial will be 6 years (scheduled duration: April 2016 to March 2022).

Our target enrollment is 250 participants (125 individuals in the control group, 125 individuals in the intervention group). No similar clinical studies exist to serve as a reference. Although the exact sample size cannot be calculated, it has been estimated as follows:

In previous studies by our group, changes in adiponectin levels had served as the primary endpoint, and the standard deviation (SD) for changes in adiponectin levels (defined as the percentage of change in adiponectin levels before and after treatment, with the adiponectin level prior to treatment representing 100%) was 20%. We envision a similar approach for the current trial, and the SD is set at 20% to compare the percentage of change in adiponectin levels in the two groups (individuals who do not receive nutritional guidance vs. individuals who do). In order to detect a 10% difference between the assigned groups (effect size: 0.5) at a two-tailed alpha level of 5%, with a power of 80% and an adjustment for multiple primary endpoints, each group will need to consist of 82 individuals. Assuming a 25% drop-out rate during follow-up, based on data amassed from the SC clinic, 110 participants would need to be enrolled in each group. In light of the aforementioned estimates and other factors for error, the required enrollment would ultimately be a total of 250 individuals who visit the SC clinic, or approximately 125 individuals in each group.

The study’s inclusion and exclusion criteria are outlined in Table 1. The participants must meet all of the inclusion criteria and none of the exclusion criteria.

**Table 1 Tab1:** Inclusion and exclusion criteria

Inclusion criteria	

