#### Items analyzed and analytical methods

The participant characteristics in both groups will be described statistically. Mean values for weight, abdominal circumference, changes in marker levels for glucose and lipid metabolism, along with changes in cardiovascular biomarkers from enrollment until 9 months after enrollment, will be compared between the two groups. The distribution of individual indices at baseline and at 9 months after enrollment will be determined for the two groups, and a *t* test or a Wilcoxon rank-sum test will be performed. In addition, Fisher’s exact test will compare the percentage of individuals who quit smoking for a prolonged period in the two groups. The level of significance will be 0.05 or less. A two-tailed alpha of 5% and a two-sided 95% confidence interval will be used. The statistical analysis will be performed by a statistician. The primary endpoint will be assessed statistically to facilitate an interim analysis. Nutritional guidance will be deemed effective or ineffective in the final analysis using the statistic *Z*_prop_ = 1.567. An interim analysis will be performed after the 125 participants (an intermediate number of individuals out of the total enrollment) complete follow-up. This interim analysis will determine whether to terminate this trial for efficacy or futility. Trial termination for efficacy will be based on *Z*_prop_ > 2.538, whereas trial termination for futility will be based on *Z*_prop_ < 0.698.

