#### Early termination of this trial

This trial will be terminated early in any of the following situations:

(1) the trial needs to be terminated for efficacy or futility based on the results of interim analysis; (2) the trial will continue based on the results of interim analysis and the target number of participants is modified or the target number of participants is reached prior to the scheduled conclusion of enrollment; (3) the Central Ethics Review Committee recommends that the trial be terminated due to serious adverse events; or (4) the Central Ethics Review Committee deems that the trial cannot be completed due to limited enrollment.

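### The stopping and success thresholds belong to a one-sided 5% design, but the plan states a two-tailed 5% test, so the false-positive rate for benefit is doubled

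*Protocol article*

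**What the plan says.** The error rate is given twice, both times as two-tailed. Under Design and sample size, the trial is sized "at a two-tailed alpha level of 5%, with a power of 80% and an adjustment for multiple primary endpoints". Under Items analyzed and analytical methods: "A two-tailed alpha of 5% and a two-sided 95% confidence interval will be used".

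That second section also sets the decision rule:

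- Timing: "An interim analysis will be performed after the 125 participants (an intermediate number of individuals out of the total enrollment) complete follow-up". This is 125 of 250, an information fraction of 0.5.
- Interim: "Trial termination for efficacy will be based on *Z*_prop_ > 2.538, whereas trial termination for futility will be based on *Z*_prop_ < 0.698".
- Final: "Nutritional guidance will be deemed effective or ineffective in the final analysis using the statistic *Z*_prop_ = 1.567".

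The section Early termination of this trial lists, as a ground for stopping, that "the trial needs to be terminated for efficacy or futility based on the results of interim analysis". A one-sided test is not mentioned anywhere.

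**The concern.** A final bar of 1.567 is too low for the stated test. A single-look two-sided 5% test needs 1.96, and even a single-look one-sided 5% test needs 1.645. Adding an interim look for efficacy normally raises the final bar. Here the bar has dropped below the single-look value, which can happen only if the design is one-sided at 5% and takes credit for the futility stop.

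The primary conclusion of the trial depends on this. If the final Z falls between 1.567 and about 1.96, the decision rule calls guidance effective, while the stated 0.05 level and the two-sided 95% confidence interval say the result is not significant. The interim bar is affected as well, so the trial could stop early on evidence weaker than the stated alpha supports.

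**Working it through.** **Inputs.** Thresholds 2.538, 0.698 and 1.567, and an interim at t = 125/250 = 0.5 (Items analyzed and analytical methods). Two-tailed alpha 5%, power 80%, standardized effect 0.5, 82 per group and 25% drop-out (Design and sample size). I take positive Z to favour guidance and a verdict of effective to mean a final Z above 1.567. Z1 and Z2 are the interim and final statistics, bivariate normal with correlation √0.5.

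**1. Reproducing the plan's thresholds.** Assume one-sided α = 0.05, β = 0.20 and binding futility.

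- Interim efficacy, O'Brien-Fleming-type spending: 2[1 − Φ(1.96/√0.5)] = 2[1 − Φ(2.772)] = 0.005575, which gives Z = 2.538.
- Interim futility, Pocock-type beta spending: 0.20 × ln(1 + (e − 1) × 0.5) = 0.1240. The drift that gives 80% power is 2.621, so the bound is Φ⁻¹(0.1240) + 2.621 × √0.5 = −1.155 + 1.853 = 0.698.
- Final: solving P(Z1 > 2.538) + P(0.698 < Z1 < 2.538, Z2 > c) = 0.05 gives c = 1.5666, i.e. 1.567.

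All three published values are recovered to three decimals, so a misprint is not a plausible explanation.

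**2. Error rate of the stated rule under no effect.**

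| Case (t = 0.5) | Computation | Result | Allowed by two-tailed 5% |
|---|---|---|---|
| Benefit, futility obeyed | 0.00557 + 0.04439 | 0.04997 | 0.025 |
| Benefit, futility overridden | 0.00557 + 0.05449 | 0.0601 | 0.025 |
| Rule read on the absolute value of Z, futility obeyed | 0.0111 + 0.0890 | 0.1002 | 0.05 |

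The nominal two-sided p at Z = 1.567 is 2 × 0.0586 = 0.117.

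**3. Role of the futility stop.** With the same spending at one-sided 5% but non-binding futility, the final value is 1.662. The fall to 1.567 comes entirely from assuming that the trial always stops below 0.698.

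**4. Same spending at two-tailed 5% (0.025 toward benefit), t = 0.5.**

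- The interim spend is 0.001525, which gives Z = 2.963.
- The final value is 1.969 with non-binding futility, or 1.920 if 0.698 is kept and binding.
- Re-deriving futility as well (Pocock-type beta spending, 80% power, binding) gives 2.963 / 0.923 / 1.881.

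None of these designs yields 2.538 at the interim.

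**5. Power with 2.963 / 0.698 / 1.969.** Drift = 0.5 × √(n/2), interim at half information, futility stop applied.

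- n = 82: drift 3.202, power 0.242 + 0.625 = 0.868.
- n = 94 (125 × 0.75 = 93.75): drift 3.428, power 0.295 + 0.613 = 0.908.

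**6. Sensitivity to interim timing.** If 25% drop out, 125 completers out of 187.5 are about 0.67 of the information. The stated rule then has an error of 0.055 (futility obeyed) or 0.059 (overridden). At t = 0.4 it is 0.046 with futility obeyed.

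**The case against.** No fair objection removes the conflict, but several limit how the correction should be stated.

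- **Information fraction.** The pair 2.963/1.969 is exact only at t = 0.5. If 94 per group are analysed, 125 completers are 62.5/94 = 0.665 of the information, and the same spending gives about 2.51 and 1.99. This stands as a reason to name the spending function as well as the numbers. It does no harm to the error rate: with 2.963/1.969 kept at about 0.67, the error toward benefit is about 0.0247.
- **Multiplicity.** The sample size text mentions an adjustment for multiple primary endpoints, and a split alpha would make the bounds stricter. The Primary endpoint section names adiponectin alone, so the full 5% is assumed here. Any split would widen the gap to the published thresholds.
- **Binding futility.** The early-termination section reads as though the stop will be obeyed, so 6.0% describes a departure from the plan. That is correct, but the figure with the stop obeyed is still 5.0%, twice what is allowed.
- **A one-sided test could be intended.** In that case the thresholds are computed correctly and the text is wrong. The plan says two-tailed in two places and promises a two-sided 95% interval, so the contradiction remains until one side is changed.

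**Conclusion.** The plan is wrong as written. The thresholds implement a one-sided 5% test with binding futility, while the text claims a two-tailed 5% test. The false-positive rate for benefit is 4.997% rather than 2.5%, and 6.0% if the futility stop is not enforced. If the rule is applied to both directions, the error is 10.0% rather than 5%. A result with a two-sided p as high as 0.117 would count as success.

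This rests on an interim at half information, on positive Z favouring guidance, and on one primary endpoint carrying the full alpha. At about 0.67 of the information the excess is slightly larger (5.5% with futility obeyed). At 0.4 it is slightly smaller (4.6%), still well above 2.5%. The correction is essential and should precede the interim analysis.

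**What to change.** Before the interim, amend the protocol (or settle it in the SAP) as follows:

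1. Replace 2.538 with 2.963 and 1.567 with 1.969, the O'Brien-Fleming-type bounds for two-sided 5% with one interim at 50% information.
2. Declare the 0.698 futility rule non-binding, so that the final bound stays valid if the trial continues past it. If the sponsor wants it binding, 1.920 is the matching final value, and the text must say that overriding it breaks the error control.
3. Name the spending function and state that the bounds will be recomputed if the interim falls at another information fraction.
4. State that the bounds assume one primary endpoint with the full alpha, or give the split.

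The alternative is to declare and justify a one-sided 5% test openly and to change the alpha and confidence interval statements in both sections to match. That route accepts a 5% chance of a false claim of benefit.

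Cost: the recommended change is a wording amendment with a harder success threshold. With the planned effect size and the interim at half information, power remains 86.8% at 82 per group and 90.8% at 94 per group, so enrollment need not change.

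### The final-analysis rule has only two labels, so missing one superiority threshold is called ineffective even when the data are inconclusive (minor)

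*Protocol article*

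**What the plan says.** All of the decision text is in the protocol article, Statistical analysis, Items analyzed and analytical methods.

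- Final verdict: "Nutritional guidance will be deemed effective or ineffective in the final analysis using the statistic", for which the single value 1.567 is given.
- Interim timing: "An interim analysis will be performed after the 125 participants (an intermediate number of individuals out of the total enrollment) complete follow-up".
- Interim boundaries: "Trial termination for efficacy will be based on *Z*_prop_ > 2.538", "whereas trial termination for futility will be based on *Z*_prop_ < 0.698".
- Inference: "A two-tailed alpha of 5% and a two-sided 95% confidence interval will be used".

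Under Design and sample size, the trial is sized on a 10-point difference in percentage change in adiponectin, and "the SD is set at 20% to compare the percentage of change in adiponectin levels in the two groups". That calculation gives 82 per group. It is then raised for a 25% drop-out rate, and target enrollment is 250.

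The article names no third outcome for the final analysis. It does not say how the confidence interval enters the verdict.

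**The concern.** A superiority test that misses its threshold has not shown that the treatment does nothing. The estimate may be close to zero and precise, or sizeable and imprecise, and the two call for different conclusions. The stated rule gives both the same label.

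The rule also does not use two things that the article already has: the two-sided 95% confidence interval, and the 10-point difference on which the trial was sized. At stake is the wording of the main conclusion. A real benefit smaller than planned could be summarised as ineffective although the data remain compatible with a useful effect. The article presents the trial as the first large randomized trial of this question, so that label could carry weight.

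**Working it through.** **Inputs.** From Design and sample size: SD 20 points, target difference 10 points, 82 per group (164 in total), 25% drop-out, 250 enrolled (250 × 0.75 = 187.5, taken as 188). From Items analyzed and analytical methods: interim at 125 completers, interim boundaries 2.538 and 0.698, final threshold 1.567.

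**Assumptions.** The article does not define the Z statistic. I take it as the standardised between-group difference in percentage change, positive in favour of guidance, with equal arms. Confidence intervals are not adjusted for the interim look.

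**1. The plan's own figure.** Take the interim at information 125/250 = 0.5. O'Brien-Fleming-type spending at one-sided 0.05 spends 0.00557 there, which gives 2.538. Treating the 0.698 futility bound as binding, the final critical value for a total one-sided alpha of 0.05 is 1.5666, that is 1.567. The threshold is therefore an efficacy boundary. Nothing in its construction tests for absence of effect.

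**2. What a near miss looks like.** SE = 2 × 20 / √N; estimate = 1.567 × SE; 95% CI = estimate ± 1.96 × SE.

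| Completers N | SE | Estimate at threshold | 95% CI | Contains 10? |
|---|---|---|---|---|
| 164 | 3.123 | +4.9 | -1.2 to +11.0 | yes |
| 188 | 2.917 | +4.6 | -1.1 to +10.3 | yes |
| 250 | 2.530 | +4.0 | -1.0 to +8.9 | no |

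**3. How wide that zone is.** The upper limit reaches 10 when Z ≥ 10/SE - 1.96.
- 164 completers: 3.202 - 1.96 = 1.24, so the zone is Z from 1.24 to 1.567.
- 188 completers: 3.428 - 1.96 = 1.47, so the zone is Z from 1.47 to 1.567.
- 250 completers: 3.953 - 1.96 = 1.99, above the threshold, so there is no such zone.

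**4. How often the label would fall on a true benefit of 5 points.** At the interim, SE = 40/√125 = 3.578 and the mean of Z is 5/3.578 = 1.398.
- Futility stop: Φ(0.698 - 1.398) = Φ(-0.700) = 24%.
- Efficacy stop: 1 - Φ(2.538 - 1.398) = 1 - Φ(1.140) = 13%.
- Trial continues and final Z is below 1.567: bivariate normal integration with correlation √(125/N) and final mean 5/SE.

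| Completers N | Final mean of Z | Final label ineffective | Futility stop | Not declared effective |
|---|---|---|---|---|
| 164 | 1.601 | 25% | 24% | 49% |
| 188 | 1.714 | 22% | 24% | 46% |
| 250 | 1.976 | 16% | 24% | 40% |

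At a true 10 points, the chance of not being declared effective is about 4% to 5% with 188 or 164 completers, and 2% with 250.

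**5. A futility stop at the boundary.** 0.698 × 3.578 = +2.5 points; 95% CI 2.5 ± 1.96 × 3.578 = -4.5 to +9.5. This excludes 10 points but not 5.

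**The case against.** The strongest reply is that *deemed ineffective* is ordinary decision language for a superiority test, that the planned 95% CI would show any imprecision, and that the wording of a non-significant result can wait for the analysis plan or the report. Much of this stands, and it is why the point is minor. It does not remove the point, because the article states the two-label rule itself and does not connect the interval to the verdict.

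Three stronger readings are tempting, and the article does not support them.

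- **That a miss will be published as proof of no effect.** The article has no publication rule and makes no claim of equivalence or absence of effect.
- **That a significantly harmful result will be called ineffective at the final analysis.** The label applies to the final analysis only, and a trial heading that way would almost always have stopped. With a true difference of -5 points, the chance of passing the futility bound and then ending below Z = -1.96 runs from about 1 in 10^8 (164 completers) to 2 in 10,000 (250). The Discussion also recognises possible harm through resumed smoking and plans to examine it.
- **That all 40% to 49% of trials at a true +5 points would be labelled ineffective.** About 24 of those percentage points are interim stops, which the article calls futility. The rest is ordinary type II error for an effect half the planned size. Rewording does not change how often it happens, only what is concluded from it.

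It is also fair to say that the zone where a near miss still contains 10 points is narrow, and that it vanishes if all 250 are analysed.

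**Conclusion.** The point holds as a minor one. The stated rule attaches an unsound label to inconclusive final results. With the article's own 25% drop-out, or with the calculated 164 completers, that includes results compatible with the full planned effect. With no loss it still includes results compatible with a moderate benefit, up to 8.9 points.

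The size rests on the planning SD of 20, equal arms, the interim at 125 completers, both interim boundaries being followed, and the assumed meaning of the Z statistic.

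This is separate from whether 1.567 fits the stated two-tailed 5% alpha. Correcting that would not remove the point: O'Brien-Fleming-type spending at one-sided 0.025 with non-binding futility gives a final value of about 1.969, which widens the range labelled ineffective.

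**What to change.** Replace the two-label sentence in Items analyzed and analytical methods with wording such as: *Guidance will be declared effective if the efficacy boundary is crossed. Otherwise the conclusion will be that efficacy was not demonstrated. In either case the estimated difference and its two-sided 95% confidence interval will be reported and used to judge which benefits or harms remain compatible with the data.* Apply the same wording after a futility stop.

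I would not add a formal category for having excluded 10 points. The article gives 10 points as a detection target and does not call it a smallest important difference. Such a category could also overlap with a declaration of efficacy: with 250 completers, Z = 1.6 crosses 1.567 while the upper limit is (1.6 + 1.96) × 2.530 = 9.0.

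The cost is one sentence in the protocol, carried into the analysis plan. Sample size, alpha, power, visits and assays are unchanged. The small downside is that the trial gives up a clean ineffective verdict.

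### The interim trigger of 125 completers is about two thirds of the expected information, but the three stated boundaries are those for one half

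*Protocol article*

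**What the plan says.** The Protocol article, *Items analyzed and analytical methods*, sets the timing of the interim: "An interim analysis will be performed after the 125 participants (an intermediate number of individuals out of the total enrollment) complete follow-up". The same paragraph gives the interim rules, "Trial termination for efficacy will be based on *Z*_prop_ > 2.538, whereas trial termination for futility will be based on *Z*_prop_ < 0.698", and the final rule, "Nutritional guidance will be deemed effective or ineffective in the final analysis using the statistic *Z*_prop_ = 1.567". It does not name the information fraction or the spending functions behind these constants.

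*Design and sample size* requires 82 evaluable participants per group (164 in total). It continues "Assuming a 25% drop-out rate during follow-up", arrives at 110 per group, and rounds the target up to 250. On timing it says "Participants will be enrolled for 3 years after the trial is approved". The endpoint visit is 9 months after enrollment.

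**The concern.** The trigger takes its number from one scale and its event from another. Half of enrollment is 125, but what has to reach 125 is the count of participants who finish follow-up, and the plan expects a quarter of those enrolled not to finish. Information for the adiponectin comparison comes from those with a 9-month value. On that scale 125 is well past the midpoint.

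Group-sequential thresholds are calculated for a particular information fraction. If the look is held at another fraction with the constants unchanged, the error rate and the stopping behavior differ from those designed. The interim is also the first listed ground for ending the trial early, so its position decides how much enrollment a stop could still spare.

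**Working it through.** **1. Reproducing the stated boundaries.** The design is inferred: two looks, Z statistics with correlation √t, O'Brien-Fleming-type alpha spending at one-sided α = 0.05, Pocock-type beta spending at β = 0.20, binding futility. At t = 0.50:

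- Alpha spent = 2[1 − Φ(1.960/√0.5)] = 0.00557, so the efficacy bound is Φ⁻¹(1 − 0.00557) = 2.538.
- Beta spent = 0.20 × ln(1 + (e − 1) × 0.5) = 0.1240. The drift that gives 80% power is 2.621, so the futility bound is Φ⁻¹(0.1240) + 2.621 × √0.5 = −1.155 + 1.853 = 0.698.
- The final bound c solves P(Z₁ > 2.538) + P(0.698 < Z₁ < 2.538, Z₂ > c) = 0.05 under the null, giving c = 1.567.

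All three printed values are returned to three decimals. Variants at t = 0.50 fail: one-sided 0.025 gives an efficacy bound of 2.963; O'Brien-Fleming-type or linear beta spending gives futility bounds of 0.316 or 0.539; no futility bound gives a final value of 1.662.

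**2. Information at the stated trigger.**

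- Expected completers: 250 × 0.75 = 187.5, so 125/187.5 = 0.667.
- Against the calculated need: 125/164 = 0.762.
- Half information is 187.5/2 = 93.75, about 94 completers (or 82 of 164).
- Sensitivity to drop-out: at 10%, 125/225 = 0.556; at 0%, 125/250 = 0.50. The mismatch comes entirely from drop-out.

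**3. Boundaries and error at each fraction.** The first three result columns apply the same spending functions at the new fraction. The last two keep 2.538, 0.698 and 1.567 unchanged and give the one-sided null probability of declaring efficacy.

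| t | Efficacy | Futility | Final | Error, futility binding | Error, futility non-binding |
|---|---|---|---|---|---|
| 0.500 | 2.538 | 0.698 | 1.567 | 5.00% | 6.01% |
| 0.667 | 2.135 | 1.120 | 1.559 | 5.49% | 5.92% |
| 0.762 | 1.964 | 1.320 | 1.558 | 5.70% | 5.88% |

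**4. Behavior under the planned effect** (d = 0.5, 93.75 evaluable per group, drift 0.5 × √(93.75/2) = 3.423, stated thresholds).

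- Chance of a futility stop: at t = 0.50, Φ(0.698 − 3.423√0.5) = Φ(−1.72) = 4.2%; at t = 0.667, Φ(0.698 − 2.795) = Φ(−2.10) = 1.8%.
- Power: 94.0% at t = 0.50 and 96.1% at t = 0.667.
- With the futility bound recomputed for 0.667, the chance is Φ(1.120 − 2.795) = Φ(−1.68) = 4.7%.

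**5. Calendar position.** This assumes even accrual of 250 over 36 months (6.94 per month); the article gives no accrual curve.

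- 125 completers need 125/0.75 = 166.7 enrolled (month 24) plus 9 months: month 33, with 229 of 250 enrolled (92%).
- 94 completers need about 125 enrolled (month 18) plus 9 months: month 27, with about 188 enrolled (75%).
- For 125 completers at 25% drop-out, the enrolled share runs from 85% (48-month accrual) to 97% (30-month accrual). With no drop-out and 36 months it is 75%.

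**The case against.** The best defense is that the parenthesis ties 125 to enrollment. If the look is held when the first 125 enrolled reach month 9, drop-outs included, about 94 have data, t is 0.50 of 187.5, and the boundaries fit. This may well have been the intention. It is not what the sentence says, which makes finishing follow-up the event; someone applying it literally would hold the look later. The reading does lower the charge from a wrong design to a trigger that is worded so that it disagrees with its own constants.

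A second defense starts from "A two-tailed alpha of 5% and a two-sided 95% confidence interval will be used". At one-sided 0.025 the same alpha-spending family gives 2.538 at t of about 0.65, close to 0.667, so the efficacy value alone does not prove one half. The other two values settle it: with a final threshold of 1.567 the one-sided error at 0.667 is about 5.5% to 5.9%, not 2.5%. Only the joint fit points to 0.50.

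Third, the harm is small, and this stands. The rise to 5.5% or 5.7% arises only because binding futility is credited in the final threshold. Without that credit the later look slightly lowers the error, and with the constants unchanged it also reduces wrongful futility stops and raises power.

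Fourth, spending functions and actual information fractions are usual analysis-plan content. That is so, and their absence from an article is not the point. The article itself prints both the trigger and the constants, and these two do not agree.

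**Conclusion.** The point holds as an internal mismatch with modest consequences. As written, the interim falls at 67% of expected information (76% against the required 164), while the thresholds are those for 50%. The excess in one-sided error is 0.5 to 0.7 percentage points if futility is binding, and nil if it is not. This rests on the article's 25% drop-out, on reading the trigger as completers, and on the inferred spending functions, which return all three printed values.

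Two stronger conclusions might be drawn, and the document does not support them. One is that the later look seriously damages error control: step 3 shows that it does not, and the larger question of a one-sided 5% boundary set beside a stated two-tailed 5% is a separate point. The other is that the interim is useless because nearly everyone will be enrolled: the 92% depends on an assumed even accrual, and even a look at half information would have about 75% enrolled.

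**What to change.** Choose one of two wordings, and adopt it before any interim comparison is seen.

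- **Move the trigger.** Hold the interim when about 94 participants have a 9-month adiponectin value, half of the 188 expected. The printed thresholds then fit. If the first 125 enrolled reaching month 9 was meant, say exactly that.
- **Keep 125 completers.** State the spending functions and recompute the efficacy, futility and final thresholds at the information fraction actually reached. Under the plan's own one-sided 0.05 spending these are about 2.13, 1.12 and 1.56 at 0.667. Whether alpha should be 0.05 one-sided at all must be settled separately, and these values would change with it.

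Either way, state the denominator of the information fraction and whether futility is binding.

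The cost is an amendment or analysis-plan wording, with no extra participants. The earlier look carries less information and, against 125 completers with unchanged thresholds, a somewhat higher chance of wrongful futility stopping (4.2% against 1.8%). Most of that difference disappears if the futility bound is recomputed for the later look (4.7%).
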